### Brisk walking group

Based on the health education group, participants in the brisk walking group will practise brisk walking under the guidance of the coach before the intervention and will then go home to practise on their own after receiving instruction. The project manager will call weekly before the intervention to urge the participants to train as needed, and the participants will self-report the training time. Subjects in the brisk walking group will engage in 12 weeks of walking training with a frequency of 3 days a week and 60 min a day, consisting of a 15 min warm-up, 40 min of walking training and a 5 min cool-down.The walking training will require subjects to walk 120–140 steps per minute, have a heart rate of 55-75% of their maximum heart rate (206.9 − 0.67*age), meet the requirements of moderate exercise intensity, and feel relaxed or free of dizziness, nausea, and fatigue [20, 29].

### Health education group

The participants in the health education group will not receive any specific exercise training in the research plan, except for fall health education before the intervention, including the factors affecting falls, the hazards of falling, and the commonly used methods of preventing falls. They will be required to maintain their original activity habits. To exclude bias from the excess activity of participants, all participants will be advised not to seek any other regular exercise and will be required to record activity during the trial period according to the previously described method [26].

### Outcome assessment

The variables in this trial will consist of basic information, primary outcomes, and secondary outcomes. The basic characteristics will be measured at baseline (1–2 weeks before randomized allocation). In addition to the MRI scans, which will be measured before and after the intervention,other primary and secondary outcomes will be measured at baseline, in the middle of the intervention period (6 weeks after randomization), at the end of the intervention period (12 weeks after randomization) and after an additional 12-week follow-up period. All primary and secondary outcomes will be assessed by the experienced staff at the People’s Hospital Baoan Shenzhen, who will be blinded to the allocation results of participants. A summary of all planned measurements for this trial is shown in Fig. 2.

### Basic information

Participants’ demographic characteristics (e.g., sex, age, education, marital status, living arrangements, occupation, and socioeconomic status) and history of disease and medication use will be collected by the recruiters using a self-designed questionnaire. The basic MoCA and Beck Depression Inventory will be assessed using the corresponding scales. Baseline measurements will be completed before randomization.

### Primary outcomes

#### Fall risk

The Fall-Risk Self-Assessment Questionnaire(FRQ) is a short, 12-item instrument specifically designed for community-dwelling seniors to assess their own fall risks [30] .The total score can be obtained by summing the total number of points for all “yes” responses (giving 2 points to questions 1 and 5 and 1 point to all other questions). Participants scoring ≥ 4 (maximum score of 14 with a minimum of 0) are considered to be indicated as having a potential fall risk. The scale has been applied to older Chinese adults with good internal consistency (Cronbach’s α = 0.724) [31].

### Secondary outcomes

#### Fall efficacy

The fall efficacy index will be assessed using the Modified Fall Efficacy Scale (MFES), which is a 14-item quantitative analysis of the fear of falling while dressing or engaging in daily activities and a simple analysis of self-presentation efficacy in older adults. The first 9 items of this assessment are indoor activities and the last 5 items are outdoor activities, each with a score from 0 to 10 (0 = no confidence at all; 5 = average confidence; 10 = sufficient confidence), for a total of 11 levels. The cumulative average score for each item is the final score [32].

### Gait assessment

Gait assessment will be assessed using the Tinetti Performance Oriented Mobility Gait Assessment(POMA-G), which includes the following subscales; initiation of gait, step length, step symmetry, step continuity, path, trunk and walking stance.Each subscale is measured as abnormal = 0 or normal = 1; in some cases, adaptive = 1 and normal = 2. The total score was 12, with higher scores indicating better mobility and balance [33].

### Balance function

Balance function will be tested using a static and dynamic balance assessment analyser (model: Bismarck Super Balance), which uses a plantar pressure sensor to accurately map the trajectory of the subject’s plantar weight shift in four positions: bipedal with eyes open, bipedal with eyes closed, unipedal with eyes open, and unipedal with eyes closed. By measuring the total trajectory length (mm), peripheral area (mm^2^), trajectory length per unit area, average centre variation in the X-axis (mm), average centre variation in the Y-axis (mm), and Romberg’s quotient, we analysed the visual adjustment coefficient, balance stability coefficient, and proprioceptive coefficient to assess the degree of visual, vestibular and proprioceptive effects on balance and finally obtained the balance index of the subjects.

The visual adjustment coefficient reflects the role of vision in posture control. The larger the value, the greater the role of vision in posture control. In contrast, in the absence of visual feedback, the balance function of the body will become worse. The balance stability coefficient reflects the stability of the body. The larger the coefficient is, the smaller the degree of shaking and the better the stability of the body.The proprioceptive coefficient reflects the function of proprioception in posture control. The larger the coefficient, the stronger the proprioceptive posture adjustment ability and the easier it is to maintain balance.

#### Lower limb muscle strength

Lower limb muscle strength will be assessed using the 5 Times Sit-to-Stand (5STS) and the Thirty-Second Sit-to-Stand Test to determine the presence or absence of lower extremity muscle weakness. A chair will be adjusted to the height of each person and will be fixed to the wall.After a researcher explained the requirements and precautions to the participant, the participant was asked to sit with his or her feet exactly flat on the ground and his or her upper limbs folded across his or her chest and then to stand up all the way and sit down again without using his or her arms.The participant will be asked to repeat this sit-to-stand action five times as quickly as possible, and the time taken to complete the five repetitions will be recorded.Then, the participant will be asked to repeat as many of the sit-to-stand actions as possible in 30 s, and the maximum number completed will be recorded. The minimum value of three trials of the 5STS and the maximum value of two trials of the 30STS will be considered the participant’s score. Once the participant is unable to perform the motion or asks to suspend the test, the test will be terminated [34, 35].

### Cognitive function

Global cognitive function will be measured using the MoCA(Fuzhou version) scale, which is a cognitive screening instrument created and validated to detect mild cognitive impairment [26]. MoCA is a brief (approximately 10 min) test that evaluates visuospatial/executive functions, naming, verbal memory registration, learning, attention, abstraction, 5 min delayed verbal memory, and orientation with a total score of 0–30 (a higher score equates to a better function).

#### Activities of daily living

Activities of daily living(ADL) will be assessed using the Barthel Index(BI), which is a widely used standard scale for assessing functional disability in ADL.The BI contains 10 projects with a total of 100 points, and the higher the score is, the better the daily life self-care ability.

#### MRI scan

To further explore the potential mechanism of Baduanjin in reducing the risk of falls in patients with MCI, this study will collect participants’ resting-state MRI data before and after the intervention. The MRI scan will be conducted in the key laboratory for magnetic resonance and multimodality imaging of Guangdong province. A Siemens Prisma 3.0 T MRI system and Siemens 64-channel head and neck coil will be used for acquiring fMRI data. The resting fMRI scanning parameters are listed as follows: TR = 2000 ms, TE = 30 ms, flip angle = 90°, slice thickness = 3.6 mm, FOV = 230 mm×230 mm, matrix = 64 × 64, voxel size = 3.6 × 3.6 × 3.6 mm3, number of slices = 37, axial slices = 35, ad phases per location = 240.

#### Safety measurements

Participants will be monitored during the intervention period for the occurrence of adverse events. Any adverse events, including exercise injury and falls, will be detailed and reported by the research assistant to the research group using an adverse event case report form (CRF). The causality concerning the Baduanjin intervention and the severity of adverse events will be evaluated. Serious adverse events will be reported to the ethics committee.

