**Methods:**

In this prospective study, outcome assessor-blind, three-arm randomized controlled trial, a total of 72 eligible participants will be randomly allocated (1:1:1) into the 12-week Baduanjin exercise intervention (60 min per session, three sessions per week), the 12-week brisk walking group(60 min per session, three sessions per week) or the 12-week health education group. Primary outcome is the Fall-Risk Self-Assessment Questionnaire(FRQ), and secondary outcomes are fall efficacy index, gait assessment, balance function, lower limb muscle strength, cognitive function, activities of daily living(ADL) and MRI scans. In addition to the MRI scans, which will be measured before and after the intervention,other primary and secondary outcomes will be assessed at baseline, 6 weeks, and 12 weeks (at the end of the intervention) and after an additional 12-week follow-up period. The mixed linear model will be conducted to observe the intervention effects.

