### Statistical analysis

The data of this study will be statistically analysed using SPSS 26.0 software. All statistical tests will be performed using a two-sided test with an α value of 0.05, and we will consider the test results statistically significant when the resulting p value is ≤ 0.05.Count data will be described using frequencies, percentages, or composition ratios. The continuous data will be described by mean ± standard deviation or median. This study will include multiple imputation for missing data and an intention-to-treat analysis. One-way ANOVA will be used for data satisfying a normal distribution, teh rank sum test will be used for those not satisfying a normal distribution, and the chi-square test will be used for count data.

Primary outcomes will be further analysed with the mixed-effect linear model with restricted maximum likelihood to determine the interaction effect between group and time. In this model, the independent variables are group (Baduanjin group, brisk walking group, and health education group), time (different measurement time points), sex, age, education level and other confounding factors, all of which will be analysed as covariates.

Preprocessing of the fMRI data was performed using the Functional Connectivity Toolbox (CONN) pipeline version 21a (www.nitrc.org/projects/conn, accessed on 5 September 2022). The preprocessing included slice-timing correction, segmentation, normalization, smoothing (Gaussian kernel = 8 mm), and bandpass filtering (0.008 to 0.08 Hz) [37]. We will implement a functional connectivity analysis of the corticocortical vestibular network based on the region of interest (ROI). The selection and specific analysis method of the corticocortical vestibular network ROI is similar to that of a previous study which was conducted in 2022 [38].

Adverse effects (AEs) will be analysed using the χ^2^ test or Fisher’s exact test. If formal statistical analyses between groups cannot be performed due to the lack of power, AEs will be tabulated and summarized using descriptive statistics.

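### Falls are recorded only as adverse events and only in the first 12 of 24 weeks, and causality is specified for Baduanjin but not for the other assigned exercise

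*Protocol article*

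**What the plan says.** All places are in the protocol article.

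- **Window.** Safety measurements: "Participants will be monitored during the intervention period for the occurrence of adverse events". Outcome assessment places the later visits "at the end of the intervention period (12 weeks after randomization) and after an additional 12-week follow-up period", so follow-up runs to week 24.
- **Falls.** Safety measurements: "Any adverse events, including exercise injury and falls, will be detailed and reported by the research assistant". The abstract's methods paragraph states: "Primary outcome is the Fall-Risk Self-Assessment Questionnaire(FRQ), and secondary outcomes are fall efficacy index". The rest of that list, and the outcome sections of the main text, contain no fall count, fall rate or proportion of fallers.
- **Causality.** Safety measurements: "The causality concerning the Baduanjin intervention and the severity of adverse events will be evaluated". No other intervention is named.
- **The other exercise arm.** Under Brisk walking group, participants are instructed by a coach and "will then go home to practise on their own after receiving instruction".
- **Analysis.** Statistical analysis plans a chi-square or Fisher comparison of adverse events, with a fallback: "If formal statistical analyses between groups cannot be performed due to the lack of power, AEs will be tabulated".
- **Withdrawal.** Withdrawal criteria and management refers to serious adverse events that are related to the research and occur in the study period. It restricts this neither to one arm nor to the intervention weeks.
- **Aims.** The discussion paragraph of the abstract says the trial will examine the effect of Baduanjin on preventing falls. The closing Discussion says its effects on falls and balance will be evaluated thoroughly.

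**The concern.** Three stated rules fit poorly with the rest of the article.

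First, falls are the event that the trial is about, but they enter only through the safety form and only while the intervention runs. A fall in weeks 13 to 24 has no stated place to be written down, and it cannot be recovered reliably later. The statements about effects on falls then rest on a self-assessed risk score from participants who know their allocation.

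Second, two arms are assigned exercise, but causality is specified for only one. An injury during unsupervised walking by an older person with MCI would have no stated relatedness judgement. The withdrawal criteria, by contrast, presuppose a judgement of relatedness to the research for any participant.

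Third, the arms differ greatly in contact. If events are noticed mainly when staff see participants, the planned comparison of adverse events between arms could partly measure contact. The likelier direction is against Baduanjin, the arm seen most often.

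**Working it through.** The article gives no expected number of falls, so there is no figure to reproduce. The check has three parts.

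**1. Observation time** (72 participants, before dropout)

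- Inside the adverse-event window: 72 × 12 = 864 person-weeks.
- Whole follow-up: 72 × 24 = 1,728 person-weeks.
- Share outside the window: (1,728 − 864) / 1,728 = 50%.

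**2. Expected fallers**

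The Background section gives about 15% of people over 65 falling in 12 months, and more than a doubling of incidence in MCI. I take 30% a year as an assumption, with a range of 15% to 40%. With a constant hazard and no treatment effect, the risk by week w is 1 − (1 − p)^(w/52).

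| Annual risk p | Risk by week 12 | Risk by week 24 | Fallers of 72 by week 12 | Fallers of 72 by week 24 | First falls after week 12 |
|---|---|---|---|---|---|
| 15% | 0.0368 | 0.0723 | 2.7 | 5.2 | 49% |
| 30% | 0.0790 | 0.1518 | 5.7 | 10.9 | 48% |
| 40% | 0.1112 | 0.2100 | 8.0 | 15.1 | 47% |

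The last column is 1 − (risk by week 12) / (risk by week 24). At 30%, each arm of 24 would have about 1.9 fallers by week 12 and 3.6 by week 24.

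*What the longer window buys.* Take p1 as the risk above, p2 = p1/2, n = 24 per arm and two-sided α = 0.05. Power is Φ[(p1 − p2 − 1.96·SE0) / SE1], where SE0 uses the pooled proportion and SE1 the separate ones. At 30% a year it rises from about 8% to 13%. At 15% it rises from about 6% to 8%, and at 40% from about 10% to 17%. The approximation is rough at such counts, but it leaves no doubt that power is very low.

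*Width of an interval.* With 2 against 4 falls, each in a different participant, and equal person-time, the rate ratio is 0.5. The standard error of its logarithm is √(1/2 + 1/4) = 0.866, and exp(1.96 × 0.866) = 5.46. The 95% interval is 0.5/5.46 to 0.5 × 5.46, or about 0.09 to 2.7.

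**3. Contact by arm during the 12 weeks**

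| Arm | Contact described |
|---|---|
| Baduanjin | 12 × 3 = 36 coach-guided sessions at two centres |
| Brisk walking | Coach instruction beforehand, home practice, self-reported training time, weekly reminder calls whose timing is unclear in the text |
| Health education | Education beforehand, no exercise training |

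All arms also attend the week 6 and 12 assessments and keep activity records. The article describes no common way of asking about adverse events. It describes assessor blinding for the primary and secondary outcomes, so that does not clearly extend to the adverse-event form.

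**The case against.** The strongest reply is that the declared objective and primary endpoint concern fall risk by questionnaire, measured to week 24. Making falls an endpoint is then a design preference, and fall counts would have little power in any case. This stands in part: the primary analysis loses nothing, and a longer window does not turn falls into a testable endpoint. It does not answer the statements that effects on falls will be evaluated, nor the safety gap in weeks 13 to 24.

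A reader might infer that the trial discards half its fall data. The documents do not support that. Falls after week 12 are not collected, so nothing is thrown away. The half is exact only for observation time; the share of falls depends on the assumed constant hazard.

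A reader might also infer that safety is compared unevenly by design. The text does not say so. Monitoring covers participants in general, severity grading is not restricted by arm, and the methods for eliciting events may be in a fuller protocol. Visits, calls and activity records could bring events to light in every arm. Uneven capture is a plausible consequence of unequal contact and no more. The descriptive fallback in Statistical analysis also makes a misleading formal test less likely, although tabulated counts would carry the same distortion.

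Finally, it may be said that the withdrawal criteria already cover relatedness in all arms and over the whole study. They concern serious events only and do not say how relatedness is judged. They conflict with Safety measurements and do not repair it.

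**Conclusion.** The point holds as three stated rules that should be changed or reconciled: a fall and adverse-event window of 12 weeks in a 24-week study, causality specified for one of two exercise arms, and a window that does not match the withdrawal criteria. A possible capture bias is a further risk; it probably runs against Baduanjin, but neither its presence nor its direction can be established from the article.

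The size is modest. Half of planned person-time has no stated recording, and 47% to 49% of first falls would be expected there. This assumes an annual risk of 15% to 40%, a constant hazard, no treatment effect and no dropout. The 15% figure is for people over 65, whereas the trial enrols from age 60 and excludes people with exercise contraindications, so the counts are only indicative. The matter affects safety reporting and any statement about actual falls. It deserves correction, but it does not threaten the primary result.

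**What to change.** 1. Extend fall and adverse-event recording to the week-24 visit, and reconcile the window in Safety measurements with that in Withdrawal criteria and management.
2. At the existing visits at weeks 6, 12 and 24, ask all three arms the same scripted questions on falls (number, injury) and other adverse events. The research assistant who completes the adverse-event form should ask them. The blinded outcome assessor should not, because an answer about an exercise injury could reveal the allocation. If staffing makes this impossible, ask only after the blinded assessments are finished.
3. Specify that relatedness is judged against the assigned exercise in both exercise arms.
4. Report falls per person-time by arm, with rate ratios and 95% confidence intervals, as an exploratory or secondary outcome. Base this on the scripted answers and not on events noticed in class. Present it descriptively.

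The cost is a few questions at visits already planned and one more table. Two limits should be acknowledged: people with MCI will recall falls over 6 to 12 weeks imperfectly, and with about 5 to 15 fallers in all by week 24 the intervals will be wide.

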### Sample size

The results of a previous systematic review showed that the standardized mean difference of the fall risk of the elderly with Baduanjin exercise intervention was − 0.59 [-0.83, -0.35] [36], which was used as a reference to calculate the sample size of the effect size of this study. The significance level will be set at α = 0.05, and the power will be 0.80. Using Gpower 3.9 software, we calculated that a sample size of at least 20 patients per group is needed, and considering a 20% drop-out rate, which means 24 patients per group, the total sample size required for this study is 72 cases.

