According to a new study published in JAMA, exercise interventions are the most effective way to lower the risk of falls in older persons [11]. A Cochrane systematic review involving 23,407 participants from 108 randomized controlled trials has provided strong evidence that exercise is helpful in reducing falls in community-dwelling older adults [12]. Due to the decline in physical strength and cognitive function in elderly individuals with MCI, it is not suitable to perform high-intensity, complex, or high-agility movements. Baduanjin is an exceptional representative from of traditional Chinese sports therapy, with the characteristics of harmony of body and mind and mutual support of body and spirit. Baduanjin movements are simple and suitable for elderly individuals with MCI to practice, and Baduanjin is practiced by a diverse group of individuals. Studies suggest that Baduanjin can significantly improve memory, executive function, and processing speed in older people [13, 14]; it can also improve balance, leg strength, and mobility and reduce the risk of falls [15–17].However, the mechanism by which Baduanjin reduces the risk of falls in MCI patients remains unclear.

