We intend to carry out a prospective, randomized controlled trial (RCT) to examine the effects and mechanisms of three months of Baduanjin training on the risk of falls in elderly individuals with MCI. The main goal of this trial is to verify the intervention effect of Baduanjin training on the risk of falls in elderly people with MCI and to explore the mechanism of Baduanjin in reducing the risk of falls in elderly individuals with MCI from the perspective of functional connectivity of the vestibular neural network.

We hypothesize that Baduanjin training could reduce the risk of falls in older adults with MCI compared with brisk walking and no specific exercise intervention. With neuroimaging, we hypothesize that differential functional connection changes will be observed between the Baduanjin training and the brisk walking group and the health education group.

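### One effect size (SMD 0.59) and one power (0.80) are stated with no contrast named, so the 0.80 cannot be taken to cover the brisk-walking hypothesis

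*Protocol article*

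**What the plan says.** The hypothesis at the end of the Background is that "Baduanjin training could reduce the risk of falls in older adults with MCI compared with brisk walking and no specific exercise intervention". That is two comparators, with neither ranked above the other.

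The Sample size section gives one effect, that the "standardized mean difference of the fall risk of the elderly with Baduanjin exercise intervention was − 0.59 [-0.83, -0.35", and describes its role: "which was used as a reference to calculate the sample size of the effect size of this study". It continues: "The significance level will be set at α = 0.05, and the power will be 0.80". The result is that "we calculated that a sample size of at least 20 patients per group is needed", raised to 24 per group and 72 in total for 20% drop-out. No test, contrast or comparator for the SMD is named. Under Statistical analysis, "All statistical tests will be performed using a two-sided test with an α value of 0.05".

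On the arms, walking is a 12-week programme of three 60-minute sessions a week, added to health education, that should "meet the requirements of moderate exercise intensity". The health education arm gets no exercise training. The Background argues that "exercise interventions are the most effective way to lower the risk of falls in older persons".

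**The concern.** Baduanjin versus walking is the contrast that would separate an effect of Baduanjin from an effect of exercise in general. The hypothesis claims superiority on it. A reader who sees a two-comparator hypothesis, three equal arms and one power will tend to assume that 0.80 applies to both comparisons.

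If walking lowers fall risk at all, the difference between Baduanjin and walking is smaller than the difference between Baduanjin and education. One SMD then cannot describe both. A non-significant walking comparison could be taken as evidence that Baduanjin is no better than walking, when the comparison had little chance of detecting a real difference.

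**Working it through.** **Inputs.** SMD 0.59, alpha 0.05, power 0.80 and 20 evaluable per group (Sample size); two-sided tests (Statistical analysis); two comparators (Background). The walking effect is not in the document and is varied by assumption.

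**1. The plan's own figure.** For two arms, the normal approximation gives n = 2(1.960 + 0.842)² / 0.59² = 15.70 / 0.348 = 45.1, so 46 per group; the exact t calculation gives 47. The stated 20 does not reproduce. A one-sided test needs 36 to 37. A three-group one-way ANOVA needs 38 (f = 0.295), 43 (means 0, 0, 0.59) or 57 (means 0, 0.295, 0.59). A value of 20 appears only under settings that the text does not state, for example a one-sided paired t-test, or a repeated-measures ANOVA with f = 0.295, two times and zero correlation. Neither is a two-sided calculation for Baduanjin against walking. This mismatch is a separate point, but it matters for apportioning the shortfall below.

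**2. What one SMD implies.** Let w be the SMD of walking against health education, on a common SD scale. If Baduanjin is 0.59 better than education, it is 0.59 − w better than walking. Both contrasts equal 0.59 only if w = 0, that is, if walking adds nothing to the education that every arm receives.

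**3. Power against walking.** Exact t with 2n − 2 degrees of freedom and noncentrality d√(n/2). At n = 20 the critical value is 2.024 and the noncentralities are 1.866, 1.399 and 0.933.

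| Assumed walking effect | d = 0.59 − w | Power, 20 per arm | Power, 47 per arm |
|---|---|---|---|
| none | 0.59 | 44.4% | 80.8% |
| a quarter of 0.59 | 0.4425 | 27.6% | 56.5% |
| half of 0.59 | 0.295 | 14.9% | 29.3% |

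**4. Splitting the shortfall at 20 per arm.** From 80% to 44.4% is 35.6 points, and this belongs to the sample-size error. The further loss due to a walking effect is 44.4 − 27.6 = 16.8 points (quarter) or 44.4 − 14.9 = 29.5 points (half). At 47 per arm, the size that fits 0.59, the loss is 80.8 − 56.5 = 24.3 or 80.8 − 29.3 = 51.5 points. So this point would remain if the sample size were right for 0.59.

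**5. Allowing for baseline adjustment.** The planned model uses repeated measures. Adjusting for baseline with an assumed correlation r turns d into d/√(1 − r²). At 20 per arm:

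- quarter: 0.511 at r = 0.5 and 0.620 at r = 0.7, power about 35% and 48%;
- half: 0.341 and 0.413, power about 18% and 25%;
- none: 0.826 at r = 0.7, power about 72%.

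**6. Precision.** At 20 per arm the unadjusted 95% CI half-width is 2.024 × √(2/20) = 0.64 SD, wider than the whole assumed effect of 0.59.

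**The case against.** The strongest reply is that the protocol never makes the claim. The Sample size section names no contrast and calls the SMD a reference. It does not say that 0.59 is expected against walking or that the walking comparison has 0.80 power. A three-group ANOVA and a group-by-time model are planned, so the calculation may have been an omnibus one. **This stands.** A reader might infer that the plan presents the walking contrast as powered at 0.80, but the text does not say so. What can be said is that the stated 0.80 is attached to no contrast and cannot be extended to this one.

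The review's comparator is also unknown. **This stands too.** If the 0.59 came from comparisons with other exercise, then the effect against education is the unspecified one, and the walking contrast still has 44% at 20 per arm, unadjusted.

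Next, it is tempting to say that the protocol contradicts itself on walking. That is too strong. The Background speaks of exercise in general and gives no estimate for walking or for the FRQ. Walkers train at home and self-report, while Baduanjin is coach-led at centres. A small walking effect is compatible with the document, and zero is the extreme case.

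Finally, the mixed model may be more efficient than a single-visit t-test. It may: with r = 0.7, no walking effect and all 24 per arm analysed, d = 0.826 reaches about 80%. That needs the most favourable value of every input. It would therefore be wrong to say that the trial cannot test the walking hypothesis, or that non-significance is certain. With a quarter or a half effect and 20 per arm, power stays at or below about 48%.

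**Conclusion.** The point holds in this limited form. One SMD and one power are stated without a contrast beside a hypothesis with two comparators, and the SMD fits both only if walking adds nothing to health education. The 0.80 cannot be taken to cover Baduanjin versus walking.

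Under an unadjusted two-sided t-test with 20 per arm, power for that contrast is 44% at best, and about 28% or 15% with the assumed walking effects. Baseline correlations of 0.5 to 0.7, also assumed, raise the last two to about 35–48% and 18–25%. The loss specific to this point is about 17 to 30 points at 20 per arm, or about 24 to 52 at 47 per arm; most of the gap from 0.80 at the planned size comes from the sample-size error. The direction follows for any positive walking effect, but its size depends on assumptions that the document cannot settle.

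**What to change.** In the Sample size section:

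- State which comparator the SMD of −0.59 refers to.
- Replace the single 0.80 with the recomputed power for each contrast at the planned size: about 44% for a contrast at 0.59, and for Baduanjin versus walking a range over stated, assumed walking effects. If baseline adjustment is credited, give the correlation used. Merely attaching the existing 0.80 to the health education contrast would not do, because 20 per arm does not give it there either.

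In the analysis and reporting text, present Baduanjin versus walking as an estimate with its 95% CI. State that a non-significant difference will not be read as equivalence, or as showing that Baduanjin is no better than walking.

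Which contrast is confirmatory is for the sponsor to decide. The cost is a few sentences and a less favourable stated power; no patients, visits or measurements are added.
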